### Recruitment

Participants will be remotely recruited and enrolled. No in-person visits are required (Figure 2). Eligible individuals will be identified through the Tobacco Treatment Research Program [79], which offers free tobacco cessation support to adult Oklahomans and assists with study recruitment [38,80-82]. Prospective participants will also be contacted by SMS text messages, email, and phone, and recruitment flyers will be posted in community locations (eg, barbershops and churches) and on social media through a geotargeted campaign focused on Black adults who smoke. Those interested can access a brief web-based eligibility screener via a QR code or direct link.

**Figure 2 figure2:**

Participant flow. REDCap: Research Electronic Data Capture.

### Study Enrollment

Study staff will contact via phone adults who meet preliminary eligibility to confirm eligibility and discuss study participation. To prevent fraudulent enrollments [83,84], participants will be asked to provide a photo of their driver’s license or ID (or other proof of address) and an image of a personal tobacco product to provide initial evidence of smoking status. Eligible and willing participants will be informed about the study and asked to acknowledge their consent with a digital signature. Following enrollment, participants will complete a baseline survey via REDCap (Research Electronic Data Capture; Vanderbilt University) [85] (refer to Multimedia Appendix 1 for a complete list of study measures), and their first semistructured phone interview will be scheduled to discuss their openness to using smartphone apps and to identify potential barriers to mHealth research participation (Table 1). After the interview, participants will receive a welcome packet with study instructions, copies of informed consent, and other signed study documentation, a reloadable Greenphire ClinCard [86], intervention equipment (smartphone, smartwatch, and Bedfont iCOquit Smokerlyzer), and NRT by mail.

**Table 1 table1:** Overview of qualitative domains covered in each interview.

Domain	Baseline interview	Exit interview
Participation in mHealth^a^ research	✓	
Understanding smartphone use and habits	✓	
History of using health apps and Bluetooth-enabled devices	✓	
History of using apps that promote smoking cessation and physical activity	✓	
Understanding preferences for smartphone apps that promote health behavior change within the Black population	✓	✓
History of quitting smoking and the methods used to quit smoking before study participation		✓
Problems with study equipment and smartphone app		✓
Overall impressions of app features		✓
Experiences using smartwatch during study participation		✓
Experiences using NRT^b^ during study participation		✓

^a^mHealth: mobile health.

^b^NRT: nicotine replacement therapy.

Upon confirming receipt of the study phone and materials, participants will complete an activation assessment in the study app, independently or with study staff. This will assess their ability to use app features, including viewing images, hearing sounds, reading text, and using the Bedfont iCOquit Smokerlyzer. Participants with an expired breath CO <6 ppm or who cannot use the Bedfont iCOquit Smokerlyzer will be withdrawn before randomization and asked to return the study phone and smartwatch. Participants can keep the NRT and Bedfont iCOquit Smokerlyzer to support their quit attempt and will be transferred to the Tobacco Treatment Research Program for cessation services. Participants who pass the activation assessment will be randomly assigned to the HealthyCells or HealthyCells+ intervention.

### Study Randomization

Participants will be stratified according to self-reported sedentary time at baseline (high: >8 h/d, medium: 4-8 h/d, and low: <4 h/d) assessed via the International Physical Activity Questionnaire [87]. Participants (n=60) will be randomized 1:1 in REDCap [85], and research staff will text each new participant a unique code (HealthyCells: 0101 and HealthyCells+: 0202) to access assigned app content.

### Standard Care

All participants will receive standard intensive tobacco treatment [66], beginning with a phone counseling session 1 week before the scheduled quit date and continuing weekly through the fourth week after the quit date. Counseling sessions will cover topics, including creating a quit plan, the health impact of tobacco, stress management, adopting lifestyle changes, developing coping strategies, and relapse prevention. In addition, participants will receive 8 weeks of combination NRT (nicotine patches+gum or lozenges) based on package-recommended dosing tailored to baseline smoking and nicotine dependence levels [88]. The first 4-week supply will be mailed, and participants can request the remaining supply through the study app as needed.

### MHBC Intervention: App Development and Pilot Testing

#### Overview

The HealthyCells app was developed using the Insight mHealth Platform [47]. All app content, including breath sample submissions, step count tracking, and interactive educational material, was presented to the African American Cancer Research Community Advisory Board at the Stephenson Cancer Center in November 2024 to solicit community feedback. This meeting was digitally recorded, and the study team reviewed transcripts to identify strengths, weaknesses, and gaps where the app content could be refined. Additional systematic usability testing will be conducted in this feasibility trial to evaluate app engagement, functionality, and acceptability among participants. Findings from this study will inform further refinements to the app in preparation for future large-scale trials to maximize its effectiveness and user experience.

#### MHBC Intervention: HealthyCells

In addition to all components of standard care described earlier, HealthyCells participants will be able to earn daily financial incentives for CO-verified smoking abstinence each day. Smoking status and identity will be assessed remotely via (1) self-reported daily smoking status, (2) CO breath sample submissions (ie, via the Bedfont iCOquit Smokerlyzer), and (3) Microsoft Azure facial recognition software; each of these assessment types has been successfully integrated into the Insight mHealth Platform [89,90]. Participants will be asked to upload a photo of themselves during the app activation phase, which will be stored as the reference photo for future identity verification. Participants will be instructed to keep their appearance consistent with the baseline photo during breath sample submissions (eg, removing or staying consistent with glasses, hats, and ponytails). During breath sample submissions, 2 photographs will be taken randomly during the exhalation phase to verify identity. Photographs will be encrypted and stored on the study server for later viewing by study staff as needed. A facial recognition mismatch will pause the delivery of incentives and will be flagged for internal review by study staff. Staff will click “thumbs up” or “thumbs down” for an identity match or mismatch, and incentives will be earned on schedule or unearned with incentive levels reset to the starting level.

To earn incentives for smoking abstinence, participants will be instructed to submit 2 breath samples each day (Figure 3). These participant-initiated assessments will appear on the home menu screen, with the first assessment appearing at the beginning of each day (based on participants’ self-reported waking hours) and the second assessment appearing 8 hours after the initial evaluation is completed. Participants will earn US $1 for each breath sample submission regardless of current smoking status. The incentive schedule used in this study is an adaptation of a low-cost incentive schedule the investigators have used in their previous and ongoing work with adults who are socioeconomically disadvantaged [38,89-91]. Participants who demonstrate abstinence (ie, self-reported abstinence that day, CO ≤6 ppm, and identity verification) on both breath sample submissions on their scheduled quit date will receive US $20 to reinforce the initiation of the quit attempt strongly. After that, abstinent participants will be rewarded US $4 per day, increasing by US $0.50 per week until US $5.50 per day is reached during the fourth week postquit date. Participants who are nonabstinent (or who do not provide a sample) will not earn an incentive that day, though they may begin earning incentives for abstinence again the next day. However, the amount will reset to the starting level of US $4 per abstinent day. Participants will earn US $7 per abstinent day during the eighth week postquit date. To gain the maximum incentives for smoking cessation (US $325), participants must report daily smoking abstinence and submit 2 breath samples each day (CO ≤6 ppm) with identity verification during all eligible assessment weeks (ie, wk 1-4 and the eighth wk postquit date).

**Figure 3 figure3:**
[figure not shown]
An example of a breath sample submission to verify smoking status.

HealthyCells intervention participants will receive a Samsung smartwatch to track their activity and a daily SMS text message about the benefits of increasing physical activity via the app (refer to the Daily Smoking Cessation Progress Report section). They will also have access to content and features that provide strategies for engaging in physical activity to aid their quit attempts (refer to the Set and Review Activity Goals section). However, HealthyCells intervention participants will not receive incentives to increase their physical activity.

#### MHBC Intervention: HealthyCells+

In addition to the small financial incentives earned for biochemically verified abstinence, HealthyCells+ intervention participants will earn small incentives for increasing physical activity (ie, daily step count) during their quit attempt. Starting on their scheduled quit date, participants will be rewarded US $0.50 per 1000 steps for every step >4000 daily steps, and they will receive a US $2.50 bonus if they walk at least 6000 steps a day. These criteria were set based on research showing Black adults walk about 4000 steps per day on average [92]. Providing incentives above this threshold will ensure the incentive protocol will not reinforce a sedentary lifestyle, and a bonus for meeting the 6000-step per day goal will reinforce higher levels of daily physical activity and greater positive health benefits [92-100]. Participants will not be incentivized beyond 10,000 steps per day, consistent with previous research showing limited additional health benefits [93,95-100]. Therefore, the maximum amount participants can earn per day for daily steps will be US $5.50 (ie, US $3.00 for 10,000 steps +US $2.50 for step goal bonus), an amount that parallels the amount participants can earn at the fourth week postquit date for daily smoking abstinence.

Participants will self-report their daily step count via an assessment on the app home menu at the end of each day (based on self-reported typical time to bed). This assessment will also ask participants to upload a picture of their step count (captured by the smartwatch; Figure 4). To promote compliance, participants will receive US $1 for each successful photo upload (up to 7 submissions/US $7/wk). Participants will not earn incentives for their self-reported step count total if an image is not uploaded. Consistent with the incentive schedule for smoking cessation, participants will earn these incentives for increasing physical activity starting on the scheduled quit date up to 4 weeks postquit date. Incentives may also be earned during the final 7 days of the intervention period (eighth wk postquit date). To gain the maximum incentives for increasing physical activity (US $255.5), participants must submit all step count photos and take 10,000 steps daily during all eligible assessment weeks (ie, wk 1-4 and the eighth wk postquit date).

**Figure 4 figure4:**
[figure not shown]
An example of a valid photo upload of activity data to verify daily step count.

### App Features

#### Overview

Several app features will be available to help participants earn incentives for abstinence and increase physical activity (Table 2 and Figure 5). Multimedia Appendix 2 provides a complete list of features and a detailed description. A summary of each feature is presented in Table 2.

**Figure 5 figure5:**
[figure not shown]
Home screens for HealthyCells (left) and HealthyCells+ (right) apps. NRT: nicotine replacement therapy.

**Table 2 table2:** Overview of app features.

App features	HealthyCells	HealthyCells+
App Instructions: provide participants with an app overview and study instructions	✓	✓
HealthyCells, Health Habits e-Book: interactive information about smoking and smoking cessation	✓	✓
Breath Sample Submission: submit breath samples using an Bedfont iCOquit Smokerlyzer to verify smoking status and facial recognition software to verify participant identity	✓	✓
Set Activity Goals: set daily steps, active time, and caloric goals	✓	✓
Review Activity Goals: review activity goals and receive feedback to adjust goals for the next day	✓	✓
Submit Step Count Photo: upload an image of activity data for independent verification of step count goals		✓
Report an NRT^a^ Side Effect: report side effects from NRT and receive assistance from study staff	✓	✓
Order More NRT: request more NRT during a quit attempt	✓	✓
Track My Rewards: displays the amount of compensation received for completed study assessments	✓	✓
Report a Problem: report a problem with study equipment or assessments	✓	✓

^a^NRT: nicotine replacement therapy.

#### Learn About the HealthyCells+ App

This feature will be accessible on the home screen at any time during the intervention and will provide an overview of the study apps and instructions for accessing them on their phone.

#### HealthyCells, Healthy Habits E-Book

Participants can access a short e-book to help them prepare for their upcoming quit attempt. Textbox 1 gives an overview of the topics covered in each chapter. On days 3 to 7 of the prequit week, participants will be informed 1 hour before self-reported typical bedtime about the availability of e-chapters. The entire e-book will be accessible on the home screen at any time after the participant’s scheduled quit date.

#### Set and Review Activity Goals

This feature will be accessible on the home screen at the beginning of each day, allowing participants to set activity goals. If a participant inputs a step goal below the recommended amount needed to receive health benefits or incentives, the app will notify them that they have selected an amount below the recommended threshold. Participants can adjust their goals before confirming. Once the participant has set their step goal, this feature will be removed from the home menu screen until the next day.

A total of 8 hours after setting their goal, an option to review their progress will appear on the app home screen. Participants self-report their current step count as indicated on their smartwatch, and the app will automatically calculate whether the participant has met their step goal set earlier in the day. The app will ask participants to rate how challenging it was to meet their current step goal, and their feedback will be used to adjust their step goal for the next day. We created a simple algorithm to set new goals based on the participant’s response dynamically: if they rate their current step goal as “not challenging,” the next day’s step goal will increase by 10%; if “just right,” it will increase by 5%; and if “very challenging,” it will decrease by 10%. For example, if a participant’s goal was 6000 steps and they found it “not challenging,” their new suggested goal would be 6600 steps. Once they review their activity progress, this feature will be unavailable on the home menu until the following day.

#### Report an NRT Side Effect

This feature will be accessible on the home screen at any time, and participants can select from a list of side effects associated with NRT that they experienced during the intervention. Only serious reported side effects will be sent to the study staff and research team via an encrypted email.

#### Order NRT

This feature will be accessible on the home screen at any time, and participants can order up to 4 weeks of additional NRT, which will be sent directly to the participant’s current mailing address.

#### Track My Rewards

Any time during the intervention, participants can track their rewards for submitting breath samples and activity photos (refer to the Study Compensation section) from the app home screen.

#### Report a Problem

From the app home screen, at any time during the intervention, participants can report any issues they have encountered during study participation via an encrypted email sent directly to the research team.

#### Return Study Materials

This menu option will appear on the app home screen after the participant has submitted their final breath sample and uploaded the final photo of their smartwatch activity data to verify their step count. Participants can access instructions about returning their study equipment via study-provided shipping materials.

#### Daily Smoking Cessation Progress Report

Each day during the intervention, participants will receive a notification from their study app 30 minutes after their self-reported wake time to complete a “Daily Smoking Cessation Progress Report.” The app will alert participants visually and audibly for 30 seconds, with a 15-minute snooze option available up to 5 times; after the fifth snooze, the assessment will be marked as missed. The assessment provides feedback on whether smoking status assessments were completed during the previous day, and participants will be asked to self-report confidence in using the Bedfont iCOquit Smokerlyzer and facial recognition. Participants will receive a reminder to use nicotine patches and gum or lozenges daily (or as needed). Participants will also be reminded to wear their smartwatch and set daily activity goals. In addition, participants will be asked to respond to 5 questions assessing sleep quality, mood, stress, energy, and focus.

### Study Compensation

Participants will earn up to US $650 in the HealthyCells condition and up to US $905.5 in the HealthyCells+ condition by earning incentives and completing various study activities (Table 3). Upon completing the enrollment call (ie, the participant is fully eligible and agrees to join the study), participants will receive US $25. Completing the baseline survey (US $50) and interview (US $50) within 72 hours will qualify them for a US $25 bonus, totaling US $125. During the intervention, participants will earn US $1 per breath sample submitted twice daily, with additional bonuses if both samples indicate smoking abstinence (CO <6 ppm), for a possible total of US $325. HealthyCells+ intervention participants will earn US $1 daily for submitting step count photos, with bonuses for exceeding 4000 steps (up to 10,000 total steps) and meeting a 6000-step goal, potentially totaling US $255.5. Completing the postintervention survey at the end of the intervention will offer US $50 and an additional US $50 for participating in the exit interview. If these 2 activities are completed within 72 hours, participants will earn a US $25 bonus, totaling US $125. Participants who return study materials will receive US $25, with an additional US $25 bonus if returned within 7 business days, totaling US $50.

Payments will be delivered via a reloadable GreenPhire ClinCard [86] once per week, with the first payout occurring after the baseline interview and the final payment after study materials are returned. This structured payment system encourages consistent engagement and ensures the timely return of valuable study materials by tying the final payment to their return. Participants can also track their earnings in real time through the app (refer to the Track My Rewards section), which adds transparency to the process.

**Table 3 table3:** Compensation amount and payment schedule for completed study activities.

Activity	Compensation (US $)	Bonus condition	Total compensation (US $)	Study condition	
				HealthyCells^a^	HealthyCells+^b^
Study enrollment^c^	25	None	25	✓	✓
Baseline survey	50	Complete both the baseline survey and interview within 72 h (US $25)	Up to 125	✓	✓
Baseline interview	50	Complete both the baseline survey and interview within 72 h (US $25)	Up to 125	✓	✓
Breath sample submission	1 per sample (2 samples/d)	Not smoking when completing breath samples (up to US $20)	Up to 325	✓	✓
Step count photo Submission	1 per photo (1 upload/d)	Per step above 4000 steps (maximum 10,000 steps; US $3); meeting 6000 step goal (US $2.50)	Up to 255.5		✓
Postintervention survey	50	Complete both the postintervention survey and baseline survey within 72 h (US $25)	Up to 125	✓	✓
Exit interview	50	Complete both the postintervention survey and baseline survey within 72 h (US $25)	Up to 125	✓	✓
Return study materials	25	Return study materials within 7 business days (US $25)	Up to 50	✓	✓

^a^The total compensation was up to US $650.

^b^The total compensation was up to US $905.5.

^c^Participants only earn US $25 if they successfully enroll in the study.

### Postintervention Assessment and Treatment Outcomes

At the eighth week postquit date, participants will complete a postintervention assessment via REDCap [85], answering questions similar to those in the baseline assessment to track changes in physical and mental health and health behaviors and to assess app impressions (Multimedia Appendix 1). A final semistructured interview will gather feedback on the app and suggestions for improvement (Table 1). The primary outcome for smoking cessation will be CO-verified, 7-day point prevalence smoking abstinence at 8 weeks postquit date, which will be assessed via smartphone-based self-report and a corroborating CO assessment. Expired CO is a valid indicator of smoking and cessation and compares favorably with cotinine and other biochemical measures [101]. Daily abstinence will be examined as a secondary outcome and defined as self-reported abstinence within the day combined with 2 breath CO sample submissions <6 ppm and identity verification. The number of days and consecutive days of CO-verified abstinence will be explored as additional outcomes. The other primary outcome will be the net change in average daily steps during the eighth week postquit date compared with average daily steps the week before the quit attempt (HealthyCells+ group only). Second, we will explore the number of total and consecutive days that ≥6000 steps were achieved as additional outcomes [102]. A valid day of observation for daily steps will be defined as (1) a smartwatch that was worn for at least 10 waking hours with (2) ≥500 steps taken within a day [103].

To ensure accurate, objective measurement of step count, study staff will pair each participant’s Samsung smartwatch with a Samsung smartphone and create a unique Samsung Health account before shipping the study materials. The Samsung Health app integrates seamlessly with the smartwatch, allowing continuous step count tracking. These data sync automatically from the watch to the app, enabling real-time data capture. Throughout the intervention, the research team will periodically access each participant’s Samsung Health account to securely export step data, which will be saved as a file for analysis. Once participants return the phone and smartwatch, the study team will directly extract step data from the smartwatch to verify and complement the app-synced step data. This dual extraction process enhances data reliability, ensuring comprehensive and objective measurement of participants’ physical activity [102]. After this extraction, the phone and smartwatch will be reset to factory settings to prepare them for use with another participant, ensuring privacy and consistency across participants.

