**Methods:**

A total of 60 Black adults who smoke (≥5 cigarettes/d) and are insufficiently physically active (engaging in <150 min of weekly moderate-intensity physical activity) will be randomly assigned to either HealthyCells intervention (incentives for smoking abstinence only) or HealthyCells+ intervention (incentives for both smoking abstinence and daily step counts). Participants will use study-provided smartphones, smartwatches, and carbon monoxide monitors for 9 weeks (1 wk prequit date through 8 wk postquit date). Feasibility will be evaluated based on recruitment rates, retention, and engagement. The primary outcomes include carbon monoxide–verified, 7-day smoking abstinence at 8 weeks postquit date and changes in average daily step count. Feasibility benchmarks include a recruitment rate of ≥5 participants per month, a retention rate of ≥75%, and a smoking abstinence rate of ≥20% at 8 weeks postquit date. Expected increases in physical activity include a net gain of 500 to 1500 steps per day compared to baseline.

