### Objectives

The purpose of this project is to explore the feasibility of an app-based MHBC intervention (HealthyCells) for Black adults who smoke and are insufficiently physically active. In addition to evidence-based tobacco cessation treatment [66], HealthyCells will incentivize daily smoking abstinence, while an enhanced version of the intervention, HealthyCells+, will also include incentives for meeting physical activity goals [36,67]. The inclusion of 2 active study conditions allows for a direct comparison to evaluate the added benefit of financial incentives for physical activity. The central hypothesis is that participants in the HealthyCells+ group will demonstrate greater increases in daily physical activity (measured via step counts) and improved smoking abstinence rates compared to those receiving smoking cessation incentives alone (HealthyCells). HealthyCells will also include an interactive educational e-book experience inspired by the documentary *Pathways to Freedom* [48,49], designed to guide individuals during their quit attempt and provide opportunities to set personalized activity goals, which can be dynamically adjusted daily to reflect current readiness. The primary aim will be to demonstrate intervention feasibility, including recruitment, retention, and adherence metrics, along with rates of carbon monoxide (CO)–verified smoking abstinence and prequit and postquit changes in physical activity.

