### Sample Size Justification

The sample size of 60 participants was chosen based on recommendations for feasibility trials [104,105], which prioritize assessing study processes, recruitment, retention, and intervention engagement rather than detecting statistically significant effects. This sample size is sufficient to evaluate key feasibility metrics, such as recruitment rates (target: ≥5 participants/mo), retention (≥75% completion), and adherence to intervention components, which are critical for planning a fully powered randomized controlled trial. In addition, this sample size allows for preliminary comparisons between the HealthyCells and HealthyCells+ groups to explore trends in CO-verified smoking abstinence and changes in daily step counts.

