### Analytic Plan

This analytic plan will focus on describing intervention feasibility. Feasibility indicators will include enrollment of all study participants within 12 months (≥5 adults enrolled/mo), retention of at least 75% of the participants at 8 weeks postquit date, achieving 20% smoking abstinence at 8 weeks postquit date (consistent with NRT and behavioral support standards) [104,105], and observing a meaningful 500 to 1500 [106,107] average daily step increase at eighth week postquit date. SAS (version 9.4; SAS Institute) [108] will be used for all statistical analyses, generating descriptive statistics to compare demographics, smoking status, and physical activity levels by treatment group. Group comparisons on participant characteristics and outcomes will use 2-tailed *t* tests for continuous variables and chi-square tests for categorical variables. Given the small sample size and pilot design (N=60), we will report all potential group differences with the α set at *P*<.20, following recommendations for pilot studies [109].

Smoking cessation will be analyzed in two ways: (1) an intention-to-treat analysis with missing data classified as smoking and (2) a completers-only analysis excluding participants with missing data. For physical activity outcomes, specifically the change in average daily step count from the baseline week to the eighth week postquit date, *t* tests will evaluate pre-post differences between groups. Days with <500 steps or <10 hours of watch wear time (indicating nonwear time or recording error) will be excluded. Participants must have at least 4 days of valid step count data to be included in the analyses.

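### The primary step-count outcome is defined in the HealthyCells+ arm only, which contradicts the between-arm hypothesis and the planned between-group test of the same change

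*Protocol article*

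**What the plan says.** All references are to the Protocol article.

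- **Outcome definition** (Postintervention Assessment and Treatment Outcomes): the second of two primary outcomes is the change in average daily steps, week 8 after the quit date "compared with average daily steps the week before the quit attempt (HealthyCells+ group only".
- **Hypothesis** (Objectives): "participants in the HealthyCells+ group will demonstrate greater increases in daily physical activity (measured via step counts" than participants who receive smoking incentives alone. On the design: "The inclusion of 2 active study conditions allows for a direct comparison to evaluate the added benefit of financial incentives for physical activity".
- **Sample size** (Sample Size Justification): "this sample size allows for preliminary comparisons between the HealthyCells and HealthyCells+ groups to explore trends", and change in daily steps is one of the two outcomes named there.
- **Analysis** (Analytic Plan): for change in average daily steps from the baseline week to week 8, t "tests will evaluate pre-post differences between groups".
- **Abstract** (Methods): the step outcome is listed among the primary outcomes simply as "changes in average daily step count", with no arm named.
- **Measurement**: in the smoking-incentive arm, "HealthyCells intervention participants will receive a Samsung smartwatch to track their activity" (MHBC Intervention: HealthyCells). The Methods Overview gives the watch to all participants. Step data are exported from each participant's Samsung Health account and extracted again from the returned watch (Postintervention Assessment and Treatment Outcomes).
- **Benchmark** (Abstract and Analytic Plan): an average gain of 500 to 1500 steps per day over baseline, as a feasibility indicator.

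**The concern.** The outcome section and the Analytic Plan describe the same quantity, with the same two time windows, but in different populations. They cannot both be followed for one primary outcome.

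The restriction also removes what randomisation provides. The arms are meant to differ only in the step incentive and the photo upload that goes with it. Both make a quit attempt with counselling and nicotine replacement, wear the watch, and have the goal-setting feature and reminders. A change measured in HealthyCells+ alone combines the incentive with the quit attempt and with any continuing effect of the shared components between the prequit week and week 8.

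At stake is the step figure carried forward to plan a larger trial. With two definitions in the document, either the one-arm change or the between-arm difference could be presented as the primary step result, and they answer different questions.

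**Working it through.** **1. The plan's own figure.** The sample size is 60 with no power calculation. It agrees with the recruitment target: 5 per month × 12 months = 60. With 1:1 allocation that is 30 per arm. At the 75% retention benchmark it is 0.75 × 30 = 22.5, so about 22 per arm. The document states no standard deviation, power or between-arm step effect, so there is no power figure to reproduce.

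**2. The passages side by side.**

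| Section | Step quantity | Arms |
|---|---|---|
| Abstract, Methods | change in daily steps, primary | not restricted |
| Objectives | greater increase in HealthyCells+ | both |
| Postintervention Assessment and Treatment Outcomes | week 8 minus prequit week, primary | HealthyCells+ only |
| Sample Size Justification | group comparison of step change | both |
| Analytic Plan | week 8 minus baseline week, t test between groups | both |

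Only the outcome definition restricts the arm, and no section gives a reason.

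**3. Whether the data force the restriction.** They do not. Step photo submission is the only step feature confined to HealthyCells+ (Table 2). It supports incentive payment and is not the source described for the outcome analysis. That source is the synced and extracted watch data: "The Samsung Health app integrates seamlessly with the smartwatch, allowing continuous step count tracking".

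**4. What each definition estimates.** Let S be the mean change both arms would show from the prequit week to week 8 without a step incentive, and I the added effect of the incentive.

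- HealthyCells+ change = S + I
- HealthyCells change = S
- Difference = I

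The restricted outcome gives S + I. The hypothesis concerns I. Without the second arm, S is unknown.

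**5. Illustration of how far the two can diverge.** The inputs below are assumptions, not document values: SD of change 2000 to 4000 steps per day, and S = 1000, the middle of the benchmark range, with I = 0. The alpha is the plan's two-sided 0.20 (z = 1.2816), with a normal approximation. The plan does not specify a one-arm test; this shows what one would give.

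- One-arm test, probability of a nominally significant increase = Φ(1000 / (SD/√n) − 1.2816)
  - n = 30: 0.927 (SD 2000) to 0.535 (SD 4000)
  - n = 22: 0.856 to 0.457
- Between-arm test with I = 0: 0.20 by construction, of which 0.10 favours HealthyCells+.

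If instead I = 1000, between-arm power = Φ(1000 / (SD·√(2/n)) − 1.2816)

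- n = 30: 0.744 to 0.377
- n = 22: 0.647 to 0.325

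The one-arm change can therefore look clearly positive when the incentive adds nothing. The contrast that answers the question is less certain, as the protocol accepts for a feasibility trial.

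**The case against.** The strongest reply is that the comparison is not lost. The only step-change analysis in the Analytic Plan is between groups, and both arms are measured. That stands. A reader might infer from the outcome definition that the trial would report steps with no comparator at all; the Analytic Plan contradicts this. The defect is in which quantity is called primary.

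Second, this is a feasibility trial. The Objectives make feasibility the primary aim, and the Sample Size Justification and the limitations say that the trial is not powered for differences. This also stands and limits the consequence. It does not remove the contradiction, because the step change is named a primary outcome.

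Third, the parenthesis may have been meant only for the 500 to 1500 step benchmark. The text does not say so, and the Analytic Plan does not confine the benchmark to one arm.

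Three further inferences are tempting but unsupported:

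- **That the restriction is what makes the benchmark uninformative about the incentive.** The benchmark is a gain over baseline and stays so if the parenthesis goes. The document never claims that meeting it shows an incentive effect.
- **That every shared component is new after baseline.** Participants already use the app and watch in the prequit week, with daily reminders, and counselling has begun. Only the quit attempt and continuing or cumulative effects remain uncontrolled.
- **That regression to the mean inflates the change.** Eligibility rests on self-reported activity minutes, not watch steps, so this is possible but not shown.

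**Conclusion.** The contradiction is real. The primary step outcome, as defined, cannot estimate the between-arm effect in the central hypothesis and cannot be what the planned between-group t test analyses. This follows from the text alone and needs no assumed number.

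The consequence is bounded. It concerns which step result is reported as primary and how it is read in an unpowered feasibility study. No confirmatory test, sample size or data collection depends on it. The probabilities in the working rest on an assumed SD of change of 2000 to 4000 and an assumed shared gain of 1000 steps. They show the direction of the problem, not its size in this trial. A one-arm mean is also more precise than a difference of two arms of equal size and variance by a factor of √2 whatever the SD, so that gap alone is no evidence of a fault here.

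**What to change.** 1. In Postintervention Assessment and Treatment Outcomes, delete the parenthesis limiting the step outcome to HealthyCells+.
2. Define the primary step outcome as the HealthyCells+ minus HealthyCells difference in change in average daily steps, week 8 against the prequit week, from the watch data of both arms. This is what the Analytic Plan already analyses.
3. Report each arm's pre-post change descriptively against the 500 to 1500 step feasibility benchmark, and state that meeting it is not evidence of an incentive effect. If the authors want the HealthyCells+ change to stay visible, this is its place.
4. Align the Abstract, Objectives, outcome section, Sample Size Justification and Analytic Plan with this definition.

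The cost is wording only. The watch data are already collected in both arms, and N = 60 is unaffected. The change should be made before step data are compared by arm, so that the choice of primary result cannot depend on them.
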